## Abstract

**Introduction:**

Due to a variety of barriers, the majority of cancer survivors do not do enough physical activity to meet current recommendations. This study will assess the feasibility of participation in parkrun walk-run events as a novel mode of community rehabilitation exercise.

**Methods:**

This protocol describes a single-arm intervention study with participants acting as their own controls. The study accepts adults diagnosed with any type of cancer, undergoing treatment or in remission. Participants must be able to walk and have medical clearance to exercise. A sample of 100 participants will be recruited across the Sunshine Coast over two years. Data will be collected over 9-months at 4 time points: Baseline (T1); after 4-weeks of usual daily activities and cancer management prior to parkrun participation(T2); after a 6-month parkrun intervention (T3); at 2-month follow-up (T4). The primary objectives are to assess the acceptability of, and adherence to, parkrun as rehabilitation exercise. Secondary outcomes include wellness, health-related quality of life, anxiety, depression, mood, physical function, parkrun metrics, dietary intake, and diet and exercise behaviour.

**Conclusion:**

This study will be the first to examine the long-term effects of parkrun as a cancer rehabilitation modality with regard to physical function, psychosocial outcomes and dietary intake.

**Trial registration:**

Australian and New Zealand Clinical Trials Registry ACTRN12623000473662 registered 09/05/2023.Approved by UniSC Human Research Ethics Committee (A221828) and the UK parkrun Research Board. Original protocol. Authors [name].

**Supplementary Information:**

The online version contains supplementary material available at 10.1186/s13102-024-00882-w.

## Background

Regular exercise for cancer survivors is strongly recommended to reduce the severity of adverse treatment effects, new cancer onset and cancer-specific and all-cause mortality [1]. Cancer survivors are patients living with cancer, either undergoing medical treatment or in remission. Between 60 and 70% of survivors do not meet the recommended levels of aerobic physical activity (PA) and nearly 90% do not meet strength training recommendations [1, 2]. The Clinical Oncology Society of Australia Position Statement on Exercise in Cancer Care [1] includes recommendations that individuals should aim towards, and maintain, weekly participation in at least 150 min of regular moderate-intensity aerobic exercise, or 75 min of more vigorous higher-intensity aerobic exercise. Strength training is also recommended two to three times per week [3, 4]. The reasons why cancer survivors are not meeting the physical activity levels are still somewhat unclear. Previous research with breast and prostate cancer patients suggests that reasons for low exercise participation rates include access issues, poor levels of baseline fitness, medical appointments and treatments, disease symptoms and treatment side effects [5–10]. These issues may also be relevant for other types of cancers. However, useful strategies for improving PA uptake and adherence have not been robustly investigated.

To prescribe appropriate, sustainable exercise for cancer survivors, we need to understand the factors that influence enjoyment and acceptance of, and adherence, to PA. Growing evidence from group exercise programs shows that social connection and support play a big role in exercise adherence [11, 12]. The established global run and walk event, parkrun, is a free community-based walk or run of 5 km, conducted in selected local parks [13, 14]. The event is monitored by volunteers who check that all participants have completed the course or have withdrawn safely. Parkrun has been endorsed by general practitioners as a way of preventing and managing chronic lifestyle conditions such as cardiac disease, hypertension and mental health conditions [13–15]. Recent research has shown that parkrun is effective for improving fitness and health in sedentary non-clinical populations, and also for individuals with heart disease and obesity [16–18]. The structure of parkrun suggests that it is a mode of physical activity that appeals to people with low fitness levels, and it provides a framework and social support that can be beneficial for people with chronic diseases and disabilities [19–21]. There is evidencefrom recent studies that parkrun participants reported more benefits from, and motivation for, parkrun as an activity, compared to other forms of exercise because it enhanced their happiness and satisfaction, they found it a real achievement, they met new people, spent more time outdoors, gained more social connections, felt part of a community and engaged more with friends who also did parkrun [18–20]. Parkrun can be self-paced and therefore has the potential to be a manageable, safe mode of exercise for individuals with low functional capacity [21]. Despite addressing many of the barriers to PA, parkrun has yet to be trialed as a mode of exercise rehabilitation for cancer survivors.

This project will investigate the feasibility of parkrun as a mode of physical activity for cancer survivors, with regard to acceptability, enjoyment and social identification for participants, and efficacy in maintaining or improving physical and functional status, and health-related quality of life (HRQoL) [16, 19, 20]. This study may provide much-needed evidence that parkrun is accessible, inclusive, supportive, safe and effective, and that it can provide real benefits for patients that can be translated to clinical practice [21, 22]. 

## Methods

### Experimental design

This feasibility study is ethically-approved (A2218280 and registered with Australian and New Zealand Clinical Trials Registry 9th May 2023 (identifier: ACTRN12623000473662) with recruitment about to start. No data has been collected and no results published. The manuscript is in accordance with SPIRIT guidelines (http://www.spirit-statement.org/spirit-statement/) for the reporting of study protocols (Table 1) and adheres to the CONSORT guidelines.

**Table 1 Tab1:** Outline measures and timeline of the study

	Enrolment	Allocation	Post Allocation				
TIMEPOINT			Baseline T1	Control Block T2	Intervention Block T3	Follow-up T4	Trial End Point
			0	4 weeks	End of 6 month parkrun block	2 months post-intervention	Post - T4
ENROLMENT:	X						
Eligibility screen	X						
Informed consent	X						
Allocation	X						
Single Group Own Controls		X					
**Assessments / Tools**							
Demographics & Clinical Characteristics			X				
Physical Function (Resting HR, BP, O2sat, 6MWT, 30-s Sit-to-Stand)			X	X	X		
Health-related Quality of Life (EORTC QLQ-30) questionnaire			X	X	X	X	
Anxiety & Depression (HADS) questionnaire			X	X	X	X	
General Physical Activity (IPAQ-SF)			X	X	X	X	
Dietary Intake (MEDAS) questionnaire			X	X	X	X	
Mood (Daylio app)			X	X	X	X	
Sleep Quality (Daylio app)			X	X	X	X	
Participant Satisfaction, Diet, Exercise behaviour, Intent Feedback Surveys					X	X	
Parkrun event Adherence					X	X	
INTERVENTIONS:							
Parkrun participation					X		

This protocol describes a single group cohort study with participants acting as their own controls [23]. The study outline and timeline is shown in Fig. 1.

**Fig. 1 Fig1:**
[figure not shown]
Study flowchart,Abbreviations: ADL, activities for daily living; PA, physical activity

We will recruit 100 cancer survivors over the age of 18, during a period of 24 months. The study will be advertised using the University of the Sunshine Coast (UniSC) news webpage, local and state cancer support groups, local parkrun sites, local oncologists, cancer care nurses and allied health professionals, radio and other media, newsletters and fliers, and relevant social media platforms. The initial recruitment phase will be for 6 weeks but we anticipate an ongoing recruitment strategy through 2024. Potential participants can contact the researchers for further information and can be sent the information sheet and a consent form. Informed consent must be given prior to study enrolment.

### Participants

All participants will be provided with a project information sheet detailing the project aims and structure and outlining the time commitment. Written consent must be given to the researchers prior to study enrolment and participation. Participants must also register with parkrun and receive their ID number prior to intervention participation. The informed consent process will continue through the study as the researchers and participants affirm procedures at each contact point of data collection. Participants are free to withdraw at any time.

### Study sites

Participant screenings, pre- and post-intervention exercise assessments and some questionnaires will be completed at the University of the Sunshine Coast Exercise Science laboratories. The parkrun events for the 6-month intervention are offered at nine parks on the Sunshine Coast: Mudjimba, Brightwater, Baringa, Harmony, Kawana, Golden Beach, Nambour, Maleny, Noosa. (Map, Supplementary file 3; park route information via parkrun Australia website: https://www.parkrun.com.au/)

### Inclusion criteria

Cancer survivors, aged 18 years or over, diagnosed with any type of cancer (e.g. breast, prostate, colorectal, blood, bone), who have medical clearance to walk and exercise, are eligible for the study. “Cancer survivor” is described as undergoing medical treatment or in remission. Participants would be classified according to the Palliative Care Outcomes Classification (PCOC); either Stage 1 (stable) or Stage 2 (unstable but not deteriorating) [24]. Participants must have given informed consent and must be registered with parkrun before start of the first walk/run event. Participants must be able to understand and communicate in English or participate with a carer/support person who can communicate in English. Finally, participants must be able to commit to the 9-month period of the study.

### Exclusion criteria

Cancer survivors are ineligible for this study if they are unable to walk, are classified by the PCOC as Stage 3 (deteriorating) or 4 (terminal) or are undergoing end-of-life care, and if they do not have medical clearance to at least walk or do other light exercise. Potential participants will also be excluded if they have a serious medical condition such as uncontrolled cardiac disease (e.g. angina, arrythmias, heart failure) [25] and/or hypertension; serious pulmonary disease where forced vital capacity (FVC) is less than 1 L; uncontrolled metabolic or renal disease; a current musculoskeletal injury that might cause pain during walking or jogging; a neurological condition that is a falls or exercise risk for participants; severe visual, and/or auditory impairment, or behavioural, cognitive or psychological disorder, that would affect understanding and complying with clear instructions or communicating with others. Patients are ineligible for the study if they cannot communicate in, or understand, English or follow verbal instructions from parkrun volunteers and/or a carer/support person who can speak English.

### Intervention

The study has a participant time commitment of 9 months, which includes 1 month of normal activities and management to establish baseline values for outcome measures, followed by 6 months of parkrun participation, and then a follow up at 2 months post-intervention. During the 6 months of parkrun, participants can complete events at their discretion. Parkrun events occur each Saturday morning but we anticipate that many participants may not be able to join in on a weekly basis due to cancer treatment cycles, symptoms, family or work commitments or poor weather. Parkrun events start at approximately 7am, and participants can walk or jog at their own pace. There is no set finish time but the events are normally completed within 2 h, allowing social gathering time afterwards.Volunteer marshals are stationed every few hundred metres along the paths to assist with directions, encouragement and for participant safety. Each participant wears their individual barcode so that their finish time is recorded electronically, captured and stored by the parkrun organisation. Individual results can be accessed by each participant.Volunteers have first aid and CPR training.Each course will have a first aid kit and automated defibrillator available and access for emergency vehicles if necessary.In the case of bad weather, an event would be cancelled.

## Outcomes

### Study objectives

This feasibility study has been developed primarily to assess the acceptability of, and adherence to, parkrun as an enjoyable exercise intervention for cancer survivors. Secondary aims are to assess the efficacy of parkrun to improve social support, HRQoL, mental health, to prevent physical and functional decline [3, 4, 26] as well as influence dietary intake [26–28]. 

We hypothesised that:

Consistent parkrun participation will improve cancer survivor engagement in physical activity, social interaction and social identity.Cancer survivors will enjoy doing parkrun events.Parkrun participants will have improved physical function, HRQoL, mental health, disease symptoms and treatment side-effects compared to baseline measures.Parkrun participation may indirectly affect the dietary intake of cancer survivors.

Outcome measures will be assessed at enrolment and initial screening [25] (baseline, T1); after 4 weeks of usual management and activities of daily living (ADL, T2); after 6 months of parkrun participation (T3); 2 months post-intervention follow-up (T4) (Fig. 1).

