### Outcome measures

*Physical function*: Resting heart rate, oxygen saturation (recorded using a pulse oximeter), resting blood pressure (standard auscultation), 6 min Walk Test (6MWT) and 30 s Sit-to-Stand test. These measures will be recorded at T1, T2 and T3. Participant rating of perceived effort (RPE) [29] will be recorded during and after the 6MWT and Sit-to-Stand test.*Quality of Life*: Assessed using the European Organization for Research and Treatment of Cancer (EORTC) Quality of Life Questionnaire (QLQ-30) [30]. This is a validated 30-question instrument used to assess different aspects contributing to HRQoL in cancer patients. Responses will be recorded at T1-T4.*Anxiety and depression*: Measured with the Hospital Anxiety and Depression Scale (HADS) [31]. This validated questionnaire consists of seven questions scoring levels of anxiety and seven assessing levels of depression. The scale takes approximately three to five minutes to complete and will be used at T1-T4.*GENERAL physical activity*: General physical and incidental activity, including ADL, and sitting time, will be assessed using the validated Short Form International Physical Activity Questionnaire (IPAQ-SF) [32] at T1-T4.*Dietary intake*: The Mediterranean Diet Adherence Screener (MEDAS) [33, 34] is a validated dietary assessment tool to determine adherence to a Mediterranean diet, which has been associated with improved health outcomes of cancer survivors. It consists of 14 questions (yes/no response) to assess the frequency of food groups included in the Mediterranean diet and will be administered at T1-T4.*Mood and sleep*: The Daylio Mood Diary basic version app is freely available for download to phone or smartwatch. The app allows daily diary entries for mood and sleep quality, and produces weekly and monthly graphs to track diary inputs. The app also allows participants to tap on icons that may contribute to mood and sleep quality e.g. food and water intake, stress, hobbies and leisure pursuits. These may contribute to parkrun adherence. Monthly graphs will be exported to the research team’s contact email by each participant, and data collated for each time point (T1-T4).*Participation satisfaction, diet and exercise behaviour, and intent*: A participant survey will be administered at T3 and T4. This consists of a checklist about eating and exercise behaviours, and participant feedback about the parkrun project during the study and 2-month follow up, including intent to change behaviours. The survey also includes a series of open-ended questions about parkrun where participants are encouraged to provide their opinions, likes and dislikes, levels of enjoyment, barriers to involvement, whether the intervention provided benefits and social support, and intention to continue with parkrun or other physical activity. For example, specific questions ask whether participants find parkrun fun and acceptable as rehabilitation exercise; whether it is easy to join in; did they meet new people (including other cancer survivors) and make new social connections; if they feel supported and incentivised to keep coming; if they feel safe participating; and is their quality of life improved.*Attendance and adherence*: Parkrun can provide the number of events attended by each participant through their national database, using the individual’s ID barcode number. Adherence will be calculated by dividing the number of events attended by each person by the number of available events in the 6-month period of the intervention and multiplying by 100 to give a percentage. If a participant does not finish an event, their time is not recorded.

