### Statistical analyses, sample size and power calculation

Numerical data from demographic, physical and scored questionnaire outcome measures will be analysed using Excel spreadsheets, IBM©SPSS version 29 and R studio [35]. Qualitative data (mood, participant feedback survey responses, participants’ attitudes towards the intervention, enjoyment, appropriateness, suitability, convenience and perceived effectiveness of the intervention) will be analysed thematically using NVivo and following the process of Braun and Clarke (2006) [36]. Comments will be read, organised and coded using an iterative framework (familiarisation; generation of initial codes; search for themes; review of themes; definition of themes and a final report). The codes will be reviewed, discussed and refined with the coding framework drawn from the data as well as being informed by the survey questions and themes highlighted in wider literature on parkrun outcomes [19, 20]. 

Participant demographic and cancer-related variables will be summarised using descriptive statistics (e.g. count or percent; mean and standard deviation). Linear mixed effect models will be used to determine the effect of parkrun participation on the proportion of participants meeting minimal PA recommendations. These models will include a random intercept for each participant, to account for the clustering of observation on each individual (i.e. measurements at baseline, 4-weeks usual activities, following 6 months of parkrun participation, and 2-month follow-up). A histogram and quantile-quantile plot of the model residuals will be used to determine whether the assumption of normally distributed errors is met. Model fit will be assessed using the adjusted R^2^ value and the model residual standard error; the most parsimonious model will be selected for inferences. Effect sizes (Cohen’s d) will be calculated where there are significant effects of time using the pooled standard deviation as the denominator.

In the case of participant attrition from the study, or if participants miss parkrun events in the 6-month intervention period, researchers will follow up with each participant individually, either through the study or at the end of the study. Reasons for reduced attendance or attrition can be gained from the participant and this information is valuable for informing the researchers of potential barriers or issues with parkrun as a mode of cancer rehabilitation exercise.

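### The plan claims improvement in social interaction, social identity and social support, but describes no measure of them before parkrun starts, so change from baseline cannot be estimated

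*Protocol article*

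**What the plan says.** Under Study objectives, the protocol article's first hypothesis is "Consistent parkrun participation will improve cancer survivor engagement in physical activity, social interaction and social identity". The same section says: "Secondary aims are to assess the efficacy of parkrun to improve social support, HRQoL, mental health". Social support is therefore an efficacy aim, while social interaction and social identity belong to a listed hypothesis. Both are worded as improvement.

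The Intervention section explains what the period before parkrun is for: "1 month of normal activities and management to establish baseline values for outcome measures". The study has one group with participants as their own controls, so the values at T1 and T2 are the only comparator.

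The social content appears under Outcome measures, in the entry on satisfaction, behaviour and intent: "A participant survey will be administered at T3 and T4". The questions described there include "whether the intervention provided benefits and social support" and "did they meet new people (including other cancer survivors) and make new social connections". In Table 1 the corresponding row, "Participant Satisfaction, Diet, Exercise behaviour, Intent Feedback Surveys", carries two marks, which agrees with T3 and T4. The statistical section says that qualitative data, including the survey responses, "will be analysed thematically using NVivo".

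**The concern.** In a single-arm, own-control study, a claim that something improves needs a value from before the intervention. The plan makes that claim for three social constructs but describes social questions only after six months of parkrun. A participant who was already well connected and one who became so through parkrun could give similar answers at T3.

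No analysis plan written later can repair this, because the missing element is data that would not have been collected. The study would end with a stated hypothesis and a stated efficacy aim that its own data could neither support nor contradict. These are not the primary objectives, but the Background gives social connection a prominent place in the case for parkrun, so readers will look for the result.

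**Working it through.** The point concerns the measurement schedule and the plan gives no figure to reproduce. The check is to list each construct in the first hypothesis and the social aim, find the measure described for it, and read off its time points from Outcome measures and Table 1.

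| Construct | Where claimed | Measure described | T1 | T2 | T3 | T4 |
|---|---|---|---|---|---|---|
| Physical activity | First hypothesis | IPAQ-SF | yes | yes | yes | yes |
| Social interaction | First hypothesis | Survey questions on new people and connections | no | no | yes | yes |
| Social identity | First hypothesis | None described | no | no | no | no |
| Social support | Secondary aim | Survey questions on support | no | no | yes | yes |

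1. **Other instruments.** Physical function is measured at T1 to T3. The QLQ-30, HADS, MEDAS and the Daylio mood and sleep diary are used at T1 to T4. The article describes them as measuring function, HRQoL, anxiety and depression, diet, and mood and sleep. None is assigned to social interaction, identity or support.

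2. **Count.** Before the intervention there are 2 time points, and 0 of them have a described social measure. After it there are 2, and both have the survey.

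3. **Contrasts available.** T3 minus T1 and T3 minus T2 cannot be formed for any of the three social constructs. T4 against T3 can be described for social interaction and support, but both points follow the parkrun block and say nothing about the starting level.

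4. **Type of question.** The social questions described ask what parkrun provided or led to. They invite a retrospective judgement and could not sensibly be put to someone who has not yet taken part, so moving the same questions to T1 would not work. The planned thematic analysis yields themes and does not estimate change.

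5. **General timing statement.** Study objectives also says in general terms that outcomes are assessed at T1 to T4. That does not supply a social baseline, because the specific entry for this survey and Table 1 both give the later timing.

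**The case against.** The strongest reply is that the plan already treats the social content as descriptive. The comparison with baseline is attached to the third hypothesis (function, HRQoL, mental health and symptoms) and not to the first. The Background groups social identification with acceptability and enjoyment, apart from efficacy for physical status and HRQoL. The abstract names no social outcome among the secondary outcomes, and the survey goes to thematic analysis. On this view the fault lies only in the wording of Study objectives, in a feasibility study whose primary purpose is acceptability and adherence.

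Much of this stands, and it makes rewording an adequate remedy. It does not remove the mismatch: Study objectives speaks of improvement for all three constructs and of efficacy for social support, and the schedule cannot deliver either.

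A second reply is that the QLQ-30, given at T1 to T4, may contain items on social life. Its items are not shown, so this cannot be checked from the article. A reader might infer that nothing social at all is asked before parkrun, but the documents support only that no T1 or T2 instrument is *described* as measuring these constructs or is assigned to them.

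Three further inferences are tempting and not supported:

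- **Diet and exercise checklist.** It sits in the same survey, so change in diet and activity might seem lost too. It is not: the MEDAS and the IPAQ-SF cover these at T1 to T4.
- **Mechanism.** A reader might say that the plan cannot test whether social connection drives adherence. That idea is background evidence; no hypothesis or analysis in the article proposes to test it.
- **No change of any kind.** A T3-to-T4 difference and participants' own perception of change can both be reported. What is unavailable is change from before the intervention.

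**Conclusion.** The point holds for the social outcomes only. Change from before parkrun in social interaction, social identity and social support cannot be estimated as scheduled: 0 of 2 pre-intervention time points have a described measure, and for social identity no described question names the construct at any of the 4 time points. The physical activity part of the first hypothesis is sound.

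No size in units of effect or precision can be attached. The documents give no social scale, standard deviation or target difference, and any confidence interval width would describe an instrument that the plan has not chosen.

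The conclusion assumes that Table 1 and Outcome measures list every instrument, and that the survey's social questions are of the kind described. The article gives some of them as examples, so the full survey may hold others, but its timing would still be T3 and T4. The matter is secondary to the primary objectives, yet worth settling before enrolment because a baseline cannot be recovered once a participant has started parkrun.

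**What to change.** **Preferred, if the claim of improvement is kept.** Add a short fixed-response measure of social support and connection to the T1 and T2 questionnaire packs, worded so that it can be answered before any parkrun. Include social identity if that part of the hypothesis stays. Repeat the measure unchanged at T3 and T4, and name T3 minus T2 as the analysis of change. Keep the existing open-ended questions for perceived benefit. The cost is a few minutes of participant time at each assessment and an ethics amendment. The article states that recruitment was about to start with no data collected, which is the point at which this is easiest; anyone already in the parkrun block would lack the new baseline.

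**Alternative.** If no measure is added, restate the social part of the first hypothesis and the social support aim as descriptive, namely perceived social benefit reported at T3 and T4. Remove the language of improvement and efficacy for these outcomes. This changes wording only and fits the thematic analysis already planned, but it gives up any estimate of social change.

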Sample size was determined via simulation methods using a random intercept model with the R package [35]. We were interested in powering the study to detect changes in exercise adherence (measured as the proportion of cancer patients meeting minimum physical activity guidelines) and used this outcome variable in simulations. Data used to create the model were informed by previous studies [8, 10]. We assumed the average proportion of cancer patients meeting minimal physical activity guidelines for aerobic exercise was 30% [37]. Time (three levels- baseline, 6-months parkrun and follow-up), body mass index (BMI) and sex (two levels- male and female) were included as fixed factors within the sample size model. A random intercept was included for each individual participant. BMI and sex were included as fixed factors as these variables can influence exercise adherence in cancer patients [8–10]. Calculations were made assuming fixed effects of 6%, 30% and 5% for sex, time and BMI respectively, and a standard deviation of the random intercept of 2%. Based on these assumptions and a type I error rate of 5%, 80 participants give approximately 80% power to detect the specific time effect of 30% increase in the proportion of participants meeting physical activity recommendations. A minimum of 100 participants will be recruited, which even allowing for potential attrition of 20 participants would still provide a minimum sample size of 80.

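### Secondary outcomes of a single-arm feasibility study are worded as efficacy hypotheses, and effect sizes are calculated only where the time effect is significant

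*Protocol article*

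**What the plan says.** All of this is in the protocol article.

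- **Study objectives.** Acceptability and adherence are primary. The next tier is worded as efficacy: "Secondary aims are to assess the efficacy of parkrun to improve social support, HRQoL, mental health", followed by physical and functional decline and diet. The third hypothesis is directional: "Parkrun participants will have improved physical function, HRQoL, mental health, disease symptoms and treatment side-effects compared to baseline measures". The diet hypothesis in the same list is more cautious and speaks only of a possible indirect effect.
- **Outcome measures.** Physical function consists of "Resting heart rate, oxygen saturation (recorded using a pulse oximeter), resting blood pressure (standard auscultation), 6 min Walk Test (6MWT) and 30 s Sit-to-Stand test". HADS has an anxiety part and a depression part. The EORTC questionnaire covers several aspects of quality of life. No measure is named as the deciding one for its domain.
- **Statistical analyses, sample size and power calculation.** The model is specified for one outcome: "Linear mixed effect models will be used to determine the effect of parkrun participation on the proportion of participants meeting minimal PA recommendations". A general sentence then says: "Effect sizes (Cohen’s d) will be calculated where there are significant effects of time". The only error rate belongs to the sample-size calculation for the physical-activity proportion: "Based on these assumptions and a type I error rate of 5%, 80 participants give approximately 80% power".
- **Limitations.** The study is described as a feasibility study without randomisation that should lead to a larger one.

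**The concern.** Two stated choices work together.

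First, the third hypothesis promises improvement across several domains, and physical function alone has five listed measures. Resting heart rate might shift while the walk test and the sit-to-stand test do not. Nothing in the wording then stops the heart-rate result from being offered as improved physical function.

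Second, an effect size is calculated only after significance. Estimates that pass such a gate are the larger ones, so the reported set is biased away from zero, and outcomes that did not change get no effect size at all. The study is meant to lead to a larger one, so selected and inflated effects are a poor basis for its planning. The Background also hopes for evidence of effectiveness that can be carried into clinical practice.

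**Working it through.** **Figure to reproduce.** The article states no error rate across the secondary outcomes, so there is none to reproduce. Its 5%, its 80 participants (100 − 20 = 80) and its 80% power all concern the physical-activity proportion. The calculation below shows what would follow under stated assumptions.

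**Inputs**
- Count, read from Outcome measures: resting heart rate, oxygen saturation, systolic and diastolic pressure, 6MWT and sit-to-stand (6); one QLQ score (1); HADS anxiety and depression (2). That is 9, roughly the scope of the third hypothesis. Adding MEDAS and sleep gives 11. Mood is left out because the statistical section treats it as qualitative. IPAQ-SF and perceived effort are also left out. The article gives no count.
- Threshold: nominal two-sided 5% for each measure (assumed).
- Correlation ρ between test statistics: not given, so a range is shown.

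**Independent tests, either direction:** 1 − 0.95^k
- k = 9: 1 − 0.630 = 37%
- k = 11: 1 − 0.569 = 43%

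**Equal correlation ρ.** Write each statistic as √ρ·T + √(1−ρ)·E, with T shared and c = 1.96. Then

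P(any) = 1 − ∫ φ(t) [Φ((c − √ρ t)/√(1−ρ)) − Φ((−c − √ρ t)/√(1−ρ))]^k dt

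| k | ρ = 0 | 0.3 | 0.5 | 0.7 | 0.9 |
|---|---|---|---|---|---|
| 8 | 33.7% | 30.0% | 25.0% | 19.1% | 11.9% |
| 11 | 43.1% | 37.5% | 30.4% | 22.3% | 13.1% |
| 13 | 48.7% | 41.8% | 33.4% | 24.1% | 13.8% |

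Nine tests lie between the first two rows. With only five tests the figure at ρ = 0.5 is 18%. Whatever the correlation, the expected number of false significant results among 11 is 11 × 0.05 = 0.55.

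**False improvements only.** The third hypothesis is directional, so each test has 2.5% in the favourable tail.
- k = 11, independent: 1 − 0.975^11 = 1 − 0.757 = 24%
- k = 9, independent: 1 − 0.975^9 = 1 − 0.796 = 20%
- k = 11, simulated, with measures scored so that improvement has the same sign: 15% at ρ = 0.5 and 9% at ρ = 0.8

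**Check with overall time tests.** Repeated-measures F tests were simulated with 80 participants, three visits for six outcomes and four visits for five (3,000 runs each). The chance of any significant result was 42%, 32% and 21% at ρ = 0, 0.5 and 0.8, close to the simpler calculation.

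**The significance gate.** Take a two-visit comparison with 80 participants as an illustration. Significance requires an observed mean change of at least about 1.96/√80 = 0.22 standard deviations of the change. If nothing truly changes, every effect that passes the gate is therefore at least that large in absolute value, although the true value is zero. The article's d uses a pooled standard deviation, so the threshold on that scale depends on the within-person correlation, but the direction of the bias does not.

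**The case against.** There is a substantial case on the other side.

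- *Multiplicity for secondary outcomes is commonly left to an analysis plan, which is not shown.* This stands. The absence of an adjustment rule from the article is not a fault in itself.
- *No sentence says that each secondary outcome is judged by an unadjusted time test.* This stands too. The model is named only for the physical-activity proportion, and the Cohen's d sentence governs when an effect size is computed, not when efficacy is claimed. Applying it to the other scored outcomes is plausible but is an inference.
- *The outcomes are ranked.* They are, with feasibility above efficacy. Only the secondary outcomes lack an order among themselves.
- *The third hypothesis joins its domains with 'and'.* Read literally, all would have to improve, which does not inflate error across domains. That answers part of the concern, but it does not settle which measure decides within a domain.
- *The study is single-arm and its limitations are disclosed.* A before-after change could not establish efficacy even with adjustment. That is a further reason to soften the efficacy wording.

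A reader might infer that the false-positive rate is 30% rather than a promised 5%. The document supports neither half of that. It promises no familywise 5%, and 30% needs both 11 tests and a correlation near 0.5, neither of which it states.

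The published efficacy wording and the significance gate remain. An adjustment in a separate plan would not by itself remove either.

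**Conclusion.** The point holds as one about stated wording and a stated reporting rule, not about a missing correction. Secondary outcomes of a single-arm feasibility study are framed as directional efficacy hypotheses without a deciding measure, and effect sizes are tied to significance.

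If 11 measures were each tested at a nominal two-sided 5%, the chance of at least one false significant result would be 13% to 43% over correlations from 0.9 to 0. False improvements alone would be about 24% if independent and 15% at 0.5. These sizes rest on an assumed count, threshold and correlation. Testing QLQ subscales separately would raise them, and fewer tests would lower them. The upward bias from the significance gate does not depend on the count or on the correlation between outcomes. It arises wherever the gate is applied.

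**What to change.** 1. In the statistical section, replace the significance-gated sentence. Report an estimated change and a standardised effect, each with a 95% CI, for every secondary outcome, significant or not.
2. In Study objectives, describe the secondary efficacy aims and the third hypothesis as exploratory, and state that no efficacy conclusion will rest on an isolated p-value.

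Naming one deciding measure per domain and testing those few with Holm's procedure is a possible alternative if a formal claim is wanted. It is a debatable trade-off, and the point does not depend on it.

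**Cost.** Wording only, with no new data or participants, and the article says recruitment had not yet begun. The price is that isolated significant secondary results can no longer be presented as evidence of efficacy.
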